# Comparison of the clinical performance of the flexible laryngeal mask airway in pediatric patients under general anesthesia with or without a muscle relaxant: study protocol for a randomized controlled trial

**DOI:** 10.1186/s13063-018-3141-2

**Published:** 2019-01-09

**Keywords:** Rocuronium, Muscle relaxant, Flexible laryngeal mask airway, Pediatric airway, Oropharyngeal leak pressure

## Abstract

**Background:**

The insertion of a laryngeal mask airway (LMA) is difficult in children due to the unique features of their airways. Muscle relaxants have been reported to facilitate LMA insertion in adults; however, there is a lack of evidence supporting this in children. This trial is designed to assess the feasibility of LMA insertion with and without the use of muscle relaxants in pediatric patients under general anesthesia.

**Methods/design:**

This is a prospective, double-blind, single-center, parallel-arm, non-inferiority, randomized controlled trial to be conducted with participants aged 2–7 years who are undergoing elective ophthalmic surgery under general anesthesia. Participants are randomly assigned to one of two groups based on whether muscle relaxants are used (MR group, *n* = 64) or not used (Saline group, *n* = 64) prior to LMA insertion. The primary outcome is the oropharyngeal leak pressure (OLP) at a fixed gas flow of 3 L/min. The secondary outcomes are intubation time for successful insertion, ease of insertion and mask bagging, intubation attempt for successful insertion, successful insertion rate on the first attempt, fiberoptic view of the LMA position, postoperative complications, and changes in hemodynamic and ventilatory parameters.

**Discussion:**

We will compare the OLPs to determine whether the muscle relaxant provides better conditions for the manipulation of the LMA. This is the first randomized controlled trial to investigate whether muscle relaxants are beneficial to the clinical performance of LMA insertion in pediatric patients under general anesthesia. This trial will be a resource for improving the process and safety of pediatric LMA insertion under general anesthesia.

**Trial registration:**

ClinicalTrials.gov, NCT03487003. Registered on 18 April 2018.

**Electronic supplementary material:**

The online version of this article (10.1186/s13063-018-3141-2) contains supplementary material, which is available to authorized users.

## Background

The use of a laryngeal mask airway (LMA) is increasing in pediatric anesthesia, because it provides less direct mechanical stimulation of the airway since it is placed above the larynx. Several studies have compared the insertion of an LMA and a tracheal tube and showed a significantly increased incidence of perioperative respiratory complications when using the tracheal tube in children [1–3]. However, LMA insertion can be more difficult in children than in adults. The unique features of the pediatric airway, including a larger tongue, a larger and floppier epiglottis, a more cephalad and anteriorly located  larynx, a more acute angle of the posterior pharyngeal wall to the floor of the mouth than in adults, and tonsillar hypertrophy may interfere with the ideal positioning of an LMA [4–7].

Neuromuscular blocking agents, also called muscle relaxants, have long been used to facilitate the insertion of airway devices. There are pros and cons, however, for the efficacy of muscle relaxants in LMA insertion. Recently, several studies have reported that muscle relaxants may facilitate the insertion of LMAs by enabling higher successful insertion rates, higher sealing pressure, lower leakage volume, and lower difficulty of insertion in anesthetized adult patients [8–10]. Conversely, Chen and colleagues showed that sealing pressure, airway pressure, insertion rates, and sore throats did not differ based on muscle relaxant administration [11]. However, these studies were all conducted in adult populations, and there has been a lack of evidence as to whether the muscle relaxants can be helpful in facilitating the insertion of an LMA in children. Therefore, we designed this randomized controlled study to test the hypothesis that the ease of insertion of an LMA would not be compromised in children without muscle relaxants compared to those given muscle relaxants prior to insertion.

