## Methods

### Study design

This prospective, single-center, parallel-arm, double-blind, randomized, non-inferiority trial was approved by the Institutional Review Board (IRB) of Daegu Catholic University Medical Center (version 1.2, reference number CR-18-027, validated on 18 April 2018) and was registered at ClinicalTrials.gov (NCT03487003) before patient recruitment. This trial is conducted in a tertiary university hospital (Daegu Catholic University Medical Center) in South Korea. We will conduct the protocol of this trial according to the Consolidated Standards of Reporting Trials (CONSORT) statement. We will follow the Standard Protocol Items: Recommendations for Interventional Trials (SPIRIT) guidelines and flow chart (Fig. 1 and Additional file 1).

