### Measurements

The primary outcome measurement is the oropharyngeal leak pressure (OLP) at a fixed gas flow of 3 L/min just before the start of surgery. Secondary outcomes are intubation time for successful insertion, ease of insertion and mask bagging, intubation attempts for successful insertion, successful insertion rate on the first attempt, hemodynamic parameter changes before and after the insertion, ventilator parameter changes such as peak inspiratory pressure (PIP) and expiratory tidal volume to set tidal volume ratio (TVe/TVs) before and at the end of surgery, the fiberoptic view of the LMA position after the successful insertion, as well as postoperative complications. Other outcomes include extubation time, eye opening time, Watcha agitation score, the Face, Legs, Activity, Cry, and Consolability (FLACC) score during the PACU stay, the amount of analgesics administered during the PACU stay, and duration of the PACU stay.

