The modified Yale Preoperative Anxiety Scale (mYPAS) is checked when the patients arrive at the preoperative waiting room with their parents before the premedication [14]. The OLP is determined by closing the expiratory valve at a fixed gas flow and then recording the airway pressure indicated by the anesthesia machine at which an audible gas leak is detected in the mouth [15]. Intubation time for successful insertion is measured from the time of opening the mouth until the time of bilateral chest auscultation and detection of capnography. The insertion attempt is stopped and mask bagging is applied when oxygen saturation falls below 90%. Failure of insertion is defined as the unsuccessful insertion of the device after three attempts. In this case, 0.3 mg/kg rescue rocuronium is administered, and another attempt to insert the LMA is made after 2 min. If an additional attempt is not possible, we will intubate the tracheal tube using direct laryngoscopy. Ease of insertion and mask bagging is subjectively graded by the investigator him/herself as easy, moderate, or difficult. Hemodynamic parameters such as the mean blood pressure and heart rate are recorded before and after the insertion. After fixation of the LMA by taping the tube over the chin, a 3.1-mm fiberoptic bronchoscope (PortalView® LF-DP; Olympus Medical Systems Co., Tokyo, Japan) is introduced just proximal to the end of the ventilator conduit, and the laryngeal view is evaluated according to the method described by Timmermann and colleagues [16]. An optimal view is defined as follows: the tip of the LMA placed behind the arytenoids, the epiglottis is visible, not folded down and not covering the airway, and the vocal cords are completely visible under the epiglottis. Any condition present that falls outside of these criteria is judged as a suboptimal position. At the end of the surgery, end-tidal sevoflurane concentration (ET sevo%), BIS, and train of four (TOF) ratio are recorded. Extubation time is defined as the time from the end of the surgery until the time of removal of the device.

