### Sample size

The primary outcome is the OLP. Just as in our study, a previous study confirmed the successful insertion of LMA as a sealing pressure (OLP) > 15 cmH_2_O [8]. We thought that a risk difference of 10% of this minimal sealing pressure would be appropriate to show the non-inferiority of non-MR group over MR group based on our clinical judgement. Therefore, we set the non-inferiority margin to 1.5. A sample size of 58 in each group is needed to achieve 80% power with an alpha of 0.025 to detect non-inferiority. The data are drawn from our pilot study with standard deviations (SDs) of 3.0 and 2.7. Anticipating a 10% dropout rate, we plan to enroll a total of 64 patients per group. The sample size is calculated using PASS software (version 15.0, NCSS, Kaysville, UT, USA).

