### Statistical analysis

Both intention-to-treat and per-protocol analyses will be performed. After testing the normality assumption using the Kolmogorov-Smirnov test, continuous variables will be expressed as the mean and the SD or the median and the interquartile range (IQR). Categorical variables will be expressed as numbers of patients and proportions.

The primary outcome (OLP) will be compared with a non-inferiority analysis. The non-inferiority of the LMA insertion without muscle relaxants (T, test) over the LMA insertion with muscle relaxant (C, active comparator) will be accepted if the upper bound of the two-sided 95% confidence interval for C-T is less than the assumed non-inferiority margin of 1.5. For secondary outcomes, continuous variables will be examined with an independent samples *t* test or the Mann-Whitney *U* test, and categorical variables will be examined with Pearson’s chi-squared test or Fisher’s exact test. All tests are two-sided, and *P* < 0.05 is considered statistically significant. A statistician who was not involved in data collection will conduct all statistical analyses using SPSS software (version 19.0, SPSS Inc., IBM, Chicago, IL, USA).

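### The stated hypothesis concerns ease of insertion, but the only non-inferiority test is on leak pressure, so the design cannot establish the hypothesis it states

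*Protocol article*

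**What the plan says.** The last sentence of the Background gives the hypothesis: "the ease of insertion of an LMA would not be compromised in children without muscle relaxants", compared with children given a relaxant first. Study design labels the trial accordingly: "This prospective, single-center, parallel-arm, double-blind, randomized, non-inferiority trial was approved by" the review board.

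Everything confirmatory is then attached to a different quantity:

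- Measurements: "The primary outcome measurement is the oropharyngeal leak pressure (OLP) at a fixed gas flow of 3 L/min just before the start of surgery".
- Sample size: "The primary outcome is the OLP", and "Therefore, we set the non-inferiority margin to 1.5". The 58 per group (64 with dropout) are derived from that margin.
- Statistical analysis: non-inferiority is accepted if the upper limit of the two-sided 95% confidence interval for relaxant minus no relaxant in OLP is below 1.5.

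The outcomes that describe insertion are secondary. Measurements lists insertion time and "ease of insertion and mask bagging, intubation attempts for successful insertion, successful insertion rate on the first attempt". Ease has its own definition: "Ease of insertion and mask bagging is subjectively graded by the investigator him/herself as easy, moderate, or difficult". Under Statistical analysis, continuous secondary outcomes get a t test or Mann-Whitney test, and "categorical variables will be examined with Pearson’s chi-squared test or Fisher’s exact test". All are two-sided at the 5% level. No margin is given for any of them.

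**The concern.** Saying that something is not compromised claims that any loss is smaller than some tolerable amount. Supporting it takes an outcome that measures the thing named, a tolerable amount fixed in advance, and an interval that excludes anything worse. The plan supplies all three for OLP and none of the last two for ease.

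The hypothesis about ease therefore has only two routes to a positive answer. One is to carry an OLP result over to ease. The other is to take a non-significant difference test as reassurance. Neither is sound. At stake is what the trial can conclude on the question it poses; the validity of the OLP comparison is not in doubt.

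**Working it through.** **1. The plan's own figure.** Inputs from Sample size: margin 1.5, SDs 3.0 and 2.7, alpha 0.025 (one-sided), power 80%. I assume a true difference of zero.

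n per group = (1.960 + 0.842)² × (3.0² + 2.7²) / 1.5² = 7.849 × 16.29 / 2.25 = 56.8, so 57 by the normal approximation. With the noncentral t distribution, power is 0.794 at 57 and 0.801 at 58. The stated 58 is reproduced. It powers a statement about OLP only.

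**2. Is OLP a measure of ease in this protocol?** Four places bear on this:

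- The Background, summarising the adult studies, lists better sealing pressure and less difficult insertion as separate effects of relaxants.
- Measurements lists ease and OLP as different outcomes and grades ease on its own three-level scale.
- OLP is read just before surgery starts. By then the mask is in place, and Intervention has the cuff inflated to 40 cmH2O. A child who needed three attempts can have the same OLP as one who needed a single attempt.
- The Discussion describes OLP as a marker of cuff pressure on the mucosa, and presents ease and insertion time as measured in addition.

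So OLP is not ease by the protocol's own definitions.

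**3. What a null difference test would tell us.** The article gives no insertion success rates, so the rates here are assumptions: 80% to 95% first-attempt success with a relaxant and a true 10-point fall without it. Two-sided 5% test, n per group:

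power = Φ{ [d − 1.96 √(2 p̄(1 − p̄)/n)] / √([p₁(1 − p₁) + p₂(1 − p₂)]/n) }

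For 90% v 80% at n = 64: d = 0.10, p̄ = 0.85. The null standard error is √(0.255/64) = 0.0631 and the alternative standard error is √(0.25/64) = 0.0625. Power = Φ[(0.10 − 0.1237)/0.0625] = Φ(−0.38) = 0.352.

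| Assumed rates | Power, 58 per group | Power, 64 per group |
|---|---|---|
| 95% v 85% | 43% | 47% |
| 90% v 80% | 32% | 35% |
| 80% v 70% | 24% | 26% |

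A real 10-point loss would thus give P ≥ 0.05 in about 53% to 76% of trials.

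**4. Precision.** If both true rates are 90%, the 95% interval half-width is 1.96 × √(2 × 0.9 × 0.1/64) = 10.4 points at 64 per group, and 10.9 points at 58. As an example, suppose 58/64 v 52/64 were observed. The difference is 9.4 points, chi-squared P = 0.13, and the 95% interval for the loss runs from −2.6 to +21.3 points. That is non-significant and still compatible with a loss above 20 points.

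**5. What a non-inferiority test on first-attempt success would need.** With equal true rates p, one-sided 0.025 and 80% power: n = 7.849 × 2p(1 − p)/margin². For an assumed 10-point margin this gives 75 (p = 95%), 142 (90%) and 252 (80%) per group. For an assumed 15-point margin it gives 34, 63 and 112.

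**The case against.** The strongest case is that the confirmatory question is clear where it counts. The Abstract, Measurements, Sample size and Statistical analysis all name OLP as primary; the decision rule is explicit; and the mismatch lies in one Background sentence that changes neither margin, alpha nor sample size. The authors also argue for OLP. The discussion part of the Abstract says OLP will be compared to judge conditions for handling the mask, and the main Discussion notes that other studies used it as a primary outcome for efficacy of insertion. Intervention makes a sealing pressure above 15 cmH2O part of the definition of successful insertion. Difference tests on secondary outcomes are ordinary in a non-inferiority trial.

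Most of this stands. It shows that OLP is a declared and defensible primary outcome and that the OLP test is intact. It does not make OLP a measure of ease, which the protocol defines and measures separately.

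A reader might infer that the plan will treat P ≥ 0.05 on the insertion outcomes as support for the hypothesis. The article does not say so. It states only the significance threshold and gives no rule for reading a non-significant secondary result. The misreading is a risk created by the wording.

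It is also fair that low power for an unpowered secondary outcome is expected, that the rates used above are assumed, that nothing was computed for the ease grade itself, and that reporting detail may sit in a fuller document that is not shown. The mismatch does not depend on that detail: the article states both the hypothesis and the tests, and they do not fit each other.

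**Conclusion.** The point holds as a mismatch between the stated hypothesis and the analysis. The trial can establish non-inferiority of seal pressure within 1.5 cmH2O. It cannot, as planned, establish that ease of insertion is not compromised, because the insertion outcomes have no margin and only difference tests.

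This conclusion rests on the article's text alone. The figures illustrate how little a null result would mean: under assumed first-attempt rates of 90% and 80%, power is about 32% to 35% with 58 to 64 per group, and across assumed relaxant-group rates of 80% to 95% it is 24% to 47%. They do not show a planning error. The sample size is reproduced and is not challenged. The issue should be corrected because it bears on what the trial may conclude, but it does not threaten the primary analysis.

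**What to change.** - Restate the Background hypothesis as non-inferiority of OLP without a relaxant, margin 1.5 cmH2O, so that it matches Sample size and Statistical analysis.
- Limit the non-inferiority conclusion to seal pressure.
- In Statistical analysis, give ease grade, attempts, first-attempt success and insertion time as between-group differences with 95% confidence intervals. Add that P ≥ 0.05 on these outcomes will not be the basis for concluding that insertion was not compromised.

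This needs wording and reporting changes only, with no new data and no extra patients. The downside is a narrower headline claim. Trial status puts recruitment from April 2018 to an expected end by April 2019, so the change should be recorded before the groups are compared.

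The alternative is to keep the ease hypothesis and prespecify a margin and interval-based test for one insertion outcome, with its power stated. That costs more. At an assumed 90% success rate, a 10-point margin needs 142 per group. A 15-point margin needs 63, which the planned 64 covers only if almost nobody drops out.

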## Methods

### Study design

This prospective, single-center, parallel-arm, double-blind, randomized, non-inferiority trial was approved by the Institutional Review Board (IRB) of Daegu Catholic University Medical Center (version 1.2, reference number CR-18-027, validated on 18 April 2018) and was registered at ClinicalTrials.gov (NCT03487003) before patient recruitment. This trial is conducted in a tertiary university hospital (Daegu Catholic University Medical Center) in South Korea. We will conduct the protocol of this trial according to the Consolidated Standards of Reporting Trials (CONSORT) statement. We will follow the Standard Protocol Items: Recommendations for Interventional Trials (SPIRIT) guidelines and flow chart (Fig. 1 and Additional file 1).

**Fig. 1 Fig1:**
[figure not shown]
SPIRIT flow diagram: schedule of enrollment, interventions, and assessments. *Including mean blood pressure and heart rate, ^†^ Including ventilator parameter changes such as peak inspiratory pressure (PIP) and expiratory tidal volume to set tidal volume ratio (TVe/TVs) before and at the end of surgery, ‡including respiratory adverse events (coughing, laryngospasm, bronchospasm, postoperative stridor, and desaturation; SpO2 <95%), gastric insufflation, excessive secretion, postoperative nausea and vomiting, sore throat and bloody tinge on the LMA surface; T_1_ at preoperative waiting area, T_2_ after the loss of consciousness is achieved, T_3_ insertion of LMA, T_4_ cessation of anesthetics, T_5_ extubation, T_6_ PACU arrival, T_7_ PACU discharge. *mYPAS* modified Yale Preoperative Anxiety Scale, *BIS* bispectral index, *ET*_sevo_ % end-tidal sevoflurane concentration, *TOF* train of four, *OLP* oropharyngeal leak pressure, *FOB* fiberoptic bronchoscopy, *FLACC* Face, Legs, Activity, Cry, and Consolability

### Participants and recruitment

Pediatric patients aged 2–7 years with an American Society of Anesthesiologists physical status (ASA PS) of 1 or 2 who are planning to undergo ophthalmic surgery under general anesthesia are enrolled. The exclusion criteria are as follows:Current upper respiratory infections or other respiratory symptomsOral or facial anomalyPoor dental conditionThose who cannot open their mouth or with limited ability to open their mouthWhen tracheal intubation is required

Eligibility is assessed by staff anesthesiologists and/or residents of our hospital. Potential participants who meet the inclusion/exclusion criteria are recruited at outpatient clinics or during preoperative visits before surgery. Since we enroll minors, we provide verbal and written information to, and obtain written informed consent from, all the legal guardians of the participants prior to any study-related procedures ([name]).

### Randomization and blinding

After recruitment, the participants are randomized to either the Saline or the MR group with a 1:1 ratio (Fig. 2) using a computer-generated random number. The random sequence is managed and kept within sealed opaque envelopes by an anesthesiologist ([name]) who is not listed in the author list (see “Acknowledgements”). When a patient is enrolled in the study, an anesthesia nurse opens a sealed envelope and prepares the study drug according to the group designation. The study drug (rocuronium 0.3 mg/kg in the MR group and saline 0.3 mg/kg in the Saline group) is prepared in a 3-cc syringe and labeled with a white sticker stating “study drug.”

### Withdrawal, dropout, and discontinuation

Participants are free to withdraw at any time during the trial at their own or their legal representative’s request. If the continuation of the trial may threaten the participant’s health, a participant can be withdrawn based on the investigators’ judgement. Reasons for withdrawal are recorded on a case report form. All data are analyzed according to the intention-to-treat principle.

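### The 1.5 cmH2O non-inferiority rule names no analysis set, so under intention-to-treat a Saline child's leak pressure obtained after rescue rocuronium can count as insertion without relaxant

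*Protocol article*

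**What the plan says.** All references are to the protocol article, Methods.

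- **Withdrawal, dropout, and discontinuation:** "All data are analyzed according to the intention-to-treat principle".
- **Statistical analysis:** "Both intention-to-treat and per-protocol analyses will be performed". The same section accepts non-inferiority if the upper limit of the two-sided 95% interval for C-T is under 1.5, where T is insertion without relaxant and C is insertion with it. It does not tie this rule to either analysis, or say that both must satisfy it.
- **Measurements, failure:** "Failure of insertion is defined as the unsuccessful insertion of the device after three attempts". What follows is not restricted to one arm: "In this case, 0.3 mg/kg rescue rocuronium is administered, and another attempt to insert the LMA is made after 2 min". The fallback is "If an additional attempt is not possible, we will intubate the tracheal tube using direct laryngoscopy".
- **Measurements, timing:** the primary OLP is read "just before the start of surgery", which is after any rescue insertion.
- **Intervention:** a sealing pressure above 15 cmH2O is one of the criteria for successful insertion. The Sample size section treats sealing pressure and OLP as the same quantity.

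**The concern.** In a non-inferiority trial, intention-to-treat is not automatically the cautious choice, because anything that makes the arms more alike helps the claim. Here a Saline child who fails three attempts receives the comparator drug before the primary outcome is read. Intention-to-treat keeps that OLP in arm T, although the stated comparison concerns insertion without relaxant. A child who ends with a tracheal tube contributes no mask OLP to the mean.

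The outcome is also linked to the event. A seal that stays at or below 15 cmH2O is one way to fail, so some of the lowest Saline values can be the ones replaced or lost.

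Per-protocol does not settle this by itself, because leaving out rescued children removes the hardest airways. With two analyses planned and no rule joining them to the margin, the plan does not say what is concluded if one passes and the other fails.

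**Working it through.** **1. Inputs.** From Sample size: margin 1.5, SDs 3.0 and 2.7, alpha 0.025, power 80%, 58 per group, 64 per group enrolled. The rescue share f in the Saline arm is an assumption, since the article gives no failure rate.

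**2. The plan's own figure.** Average-variance SD = sqrt((3.0² + 2.7²)/2) = sqrt(8.145) = 2.854. With a true difference of 0, the normal approximation gives n = (1.960 + 0.842)² × (9 + 7.29)/1.5² = 56.8, so 57 per group. The noncentral-t calculation gives power 0.794 at 57 and 0.801 at 58. The stated 58 is reproduced, and the sample size is not in question.

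**3. Dilution under intention-to-treat.** Let the true no-relaxant deficit equal the margin, C-T = 1.5. Let a share f of Saline children be rescued and reach the MR mean, with the SDs unchanged. The difference that intention-to-treat sees is 1.5(1 − f).

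SE = sqrt((9 + 7.29)/58) = 0.530.

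False acceptance = Φ(1.5f/0.530 − 1.96).

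| f (assumed) | Saline children of 64 | ITT difference | Normal, 58 per group | Noncentral t, 64 per group |
|---|---|---|---|---|
| 0 | 0 | 1.500 | 2.50% | 2.50% |
| 2% | 1.3 | 1.470 | 2.85% | 2.87% |
| 5% | 3.2 | 1.425 | 3.45% | 3.50% |
| 10% | 6.4 | 1.350 | 4.68% | 4.80% |
| 20% | 12.8 | 1.200 | 8.17% | 8.54% |

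**4. Neither set is safe alone.** Assume that 5% of Saline children would fail with an OLP 5 below the MR mean, and that the overall true deficit is 1.5.

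- The other 95% have a deficit of (1.5 − 0.05 × 5)/0.95 = 1.316. Per-protocol without the failures sees this value.
- Intention-to-treat, with the failures rescued to the MR mean, sees 0.95 × 1.316 = 1.25.
- By noncentral t, false acceptance is about 7.1% under intention-to-treat (64 per group) and 5.4% under per-protocol (60 per group).

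Both exceed 2.5%. This is why the fix includes an analysis that keeps the failures in their randomised arm as failures.

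**The case against.** - **The two sections can be read together.** The first sentence closes a paragraph on withdrawals, and the second can be taken as intention-to-treat plus an added per-protocol analysis. A reader might infer that the plan contradicts itself on the primary analysis; the text does not force that. The tension lies in the word covering all data. The open acceptance rule remains on either reading.
- **A fuller document may define the sets.** That covers definitions of analysis sets and missing-data detail. But the article states the decision rule down to interval, bound and margin, and leaves out which analysis it applies to.
- **Rescue and intubation are open to both arms, and intention-to-treat estimates a legitimate strategy** of starting without relaxant and rescuing if needed. Both points stand. The bias is therefore not certain in direction: it favours non-inferiority only if failures are commoner in the Saline arm, and it is a bias for the question as the plan words it.
- **Failures may be rare.** Insertion is by experienced board-certified anesthesiologists in deeply anesthetized children. At f = 2% the excess is about a third of a percentage point.
- **Selective choice of analysis.** A reader might infer that the investigators are free to pick the favourable result. The plan commits to both analyses and gives them to a statistician who did not collect data, so this goes too far. What is missing is the rule for discordant results.
- **The exclusion for required tracheal intubation.** A reader might infer that it removes intubated children after randomisation. It stands among the eligibility criteria, which are applied at clinic or preoperative visits, so it gives no support to this point.

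**Conclusion.** The point holds and should be fixed, although it does not invalidate the design. The acceptance rule is tied to no analysis set. Followed as written, intention-to-treat counts relaxant-assisted OLPs as insertion without relaxant and pulls C-T toward zero by the factor (1 − f).

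At a true deficit of 1.5, false acceptance rises from 2.5% to between 2.85% and 8.2% for f from 2% to 20%. These figures rest on two assumptions that the documents neither support nor exclude: the value of f, and full recovery of rescued children to the MR mean. They also take Saline-arm rescue as the only source of distortion. They illustrate the mechanism and do not predict its size in this trial; if three-attempt failures are rare, the effect is small.

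**What to change.** 1. Align the sentence in the withdrawal section with the statistics section, so that both name intention-to-treat and per-protocol.
2. Add to the acceptance rule that non-inferiority is claimed only if the upper bound for C-T is below 1.5 in both analyses.
3. State that Saline children given rescue rocuronium are excluded from the per-protocol set.
4. Prespecify a sensitivity analysis that keeps rescued and intubated children in their randomised arm as failures, for example a worst-rank comparison of OLP. It does not test the 1.5 margin, so it is read beside the main result.

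A fixed imputed value is not a good substitute. Since success needs a seal above 15 cmH2O, 15 is the most lenient value compatible with seal failure, and it has no basis when insertion fails on another criterion. An OLP before rescue is not a planned measurement.

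**Cost:** wording only, with no extra patients or measurements and no change to the rescue rule, on which this point takes no position. The claim becomes slightly stricter. At a true difference of 0, power is 83.9% with 64 per group and 80.1% with 58. Power to pass both analyses cannot exceed the smaller of the two, but the sets overlap heavily, so the loss should be small if few children are excluded. The wording should be settled before unblinding.
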